### Aim 2: Develop and Test the Accuracy of a New Model to Predict Appropriate Hospital Admission for an ED Patient with Bronchiolitis

We will use clinical, administrative, and environmental variable attributes to build machine learning models to predict appropriate hospital admission for individual ED patients with bronchiolitis.

#### Data Pre-Processing

Traditional techniques like imputation will be used to handle missing values and identify and correct/remove invalid values [36,51]. In the case of environmental variables, classic methods [40,41] will be used to extract aggregate values (eg, daily average) from raw values. In the case of clinical and administrative attributes, grouper models like the diagnostic cost group system will be used to aggregate diseases, drugs, and procedures to reduce attributes [52].

#### Input Variables

For ED patients with bronchiolitis, predictors of hospital admission have not been exhaustively identified. We compiled in our recent paper [39] a comprehensive list of known predictors. Some of these known predictors (eg, atopic dermatitis [53], low dew point [54], duration of respiratory distress [7], absence of familial atopy [55], enterovirus infection [55], etc) have not been used in existing predictive models for ED patients with bronchiolitis. All known predictors stored in the Intermountain Healthcare EDW and environmental data sets will be used as input variables (ie, independent variables). In addition, our data sets contain attributes beyond known predictors. We will use classic feature selection techniques [56] like the information gain method to find attributes likely to be predictive of appropriate admission. Our team’s clinical experts will review attributes, select attributes with face validity, and add these as input variables. With more new predictors of appropriate hospital admission and larger sample size, we anticipate higher prediction accuracy.

#### Predictive Models

We will use Weka [56] to construct predictive models. Weka is a widely used open-source machine learning toolkit. It integrates a large set of standard machine learning algorithms and feature selection techniques. Both categorical and numerical variables exist in administrative, clinical, and environmental data. Supervised machine learning algorithms that can deal with both categorical and numerical variables, such as *k*-nearest neighbor and random forest, will be used. We will examine each applicable algorithm and tune hyper-parameters manually.

The classic area under the receiver operating characteristic curve (AUROC) [56] performance metric will be used. Our target will be models achieving an AUROC larger than or equal to 0.9, which is considered outstanding discrimination [57]. Some machine learning models, such as decision tree and k-nearest neighbor (ie, similar patients), can be more easily interpreted [58,59]. Other machine learning models, such as random forest, are less straightforward to interpret. If accuracies of models are comparable (AUROC ≥0.9 and ≤0.02 worse for interpretable models compared to less interpretable models), we will favor those that clinicians can more easily interpret.

#### Sample Size Justification and Performance Evaluation

We have 10 years of data. We will train and test predictive models using a standard method. We will perform stratified 10-fold cross validation [56] on the initial 9 years of data to train predictive models and provide estimates of their accuracy. Data from the tenth year will be used to evaluate performance of the best-performing machine learning algorithm, reflecting use in practice. To figure out the environmental variable, administrative, and clinical attributes necessary for high accuracy, we will use backward elimination [36] to remove input variables so long as the AUROC does not decrease by more than 0.02 or go below 0.9.

No AUROC achieved by current care has been reported before. By extrapolating from statistics reported in the literature (unnecessary admissions up to 29% and unsafe ED discharges of 6%), we anticipate the AUROC achieved by current care to be between 0.6 and 0.8+ [20-24,27]. We will test the hypothesis that the model’s prediction will be more accurate by a difference in AUROC of larger than or equal to 0.05. The dependent variable has 2 possible values: appropriate hospital admission and appropriate ED discharge. Assuming a correlation coefficient of 0.6 between the model’s prediction result and the actual disposition decision for both values and using a 1-sided Z-test at a 0.05 significance level, a sample size of 356 instances per possible value of the dependent variable will have 90% power to detect an AUROC increase of 0.05. Data from the tenth year include 3615 ED visits for bronchiolitis, which provides adequate power for testing our hypothesis.

Based on 2 prior studies’ results, we anticipate that our model will achieve an AUROC larger than or equal to 0.9 and outperform current care in making disposition decisions. Neither prior study on predicting a bronchiolitis patient’s ED disposition is similar to our study, which uses appropriate admission as the gold standard. The first study [21] used actual admission as the gold standard and achieved an AUROC of 0.87. The second study [34] used judgment of an attending pediatrician as well as a length of stay longer than 1 day as the gold standard. The predictive model achieved 81% accuracy, better than an average admitting resident’s disposition decision.

For ED patients with bronchiolitis, 17 known predictors of hospital admission (Table 1) are consistently recorded at Intermountain Healthcare facilities and available as structured attributes in our data sets, along with many other potential predictors. We will start building our model using structured attributes. If the model cannot achieve high prediction accuracy, we will extract additional de-identified input variables from ED clinical notes by conducting medical natural language processing on the HIPAA-compliant Homer computer cluster at the University of Utah [60]. For instance, additional input variables include the 8 known predictors of hospital admission (Table 1) that are inconsistently recorded in clinical notes at Intermountain Healthcare facilities.

**Table 1 table1:** The list of known predictors of hospital admission for ED patients with bronchiolitis recorded at Intermountain Healthcare facilities.

Category	Predictors
The known predictors that are consistently recorded at Intermountain Healthcare facilities and available as structured attributes in our data sets	SpO_2_, heart rate, respiratory rate, temperature, age, gender, prior hospitalization, prior intubation, abnormal chest x-ray, low dew point (from the environmental variable data set), rhinovirus infection, coinfection, dehydration, history of bronchopulmonary dysplasia, history of eczema, prematurity, maternal/passive smoking
The known predictor that is rarely recorded as structured attributes at Intermountain Healthcare facilities	enterovirus infection
The known predictors that are inconsistently recorded in clinical notes at Intermountain Healthcare facilities	increased work of breathing, poor feedings, decreased feeding, breastfed, abnormalities on auscultation, retractions, family history of atopy, fewer albuterol in the first hour

If our model still cannot reach high prediction accuracy on the entire group of ED patients with bronchiolitis, we will conduct subanalyses to identify subgroups of ED patients with bronchiolitis on which our model performs well. In this scenario, we will apply our final model only to the identified subgroups of patients. These subgroups are identified by certain characteristics, such as comorbidity, prematurity, age, or ED arrival time (eg, daytime vs night, weekday vs weekend) that are typically independent variables in the original model.

We have large data sets. If scalability is a problem with Weka, a parallel machine learning toolkit like Spark’s MLlib [61] will be adopted to develop predictive models on the secure Homer computer cluster [60].

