## Introduction

Bronchiolitis is inflammation of the bronchioles, the smallest air passages in the lungs, primarily seen in children less than age 2. Within the first year of life, 10% of children are diagnosed with bronchiolitis [1]. By age 2, more than a third of children have had a bronchiolitis diagnosis [2]. Bronchiolitis causes about 71 hospitalizations and 77 emergency department (ED) visits per 1000 infant years [3]. In the United States, each year bronchiolitis incurs around 287,000 ED visits [4], 128,000 hospitalizations [5], and $1.73 billion in total inpatient costs (2009) [5]. For children under age 2, bronchiolitis is the most common cause of hospitalization and represents 16% of all hospitalizations [5-8].

Despite the huge burden of bronchiolitis care, hospitalization decisions are made with insufficient evidence [7,9], resulting in variable admission rates [1,6,9-19]. About 32%-40% of ED patients with bronchiolitis are admitted to the hospital [20-22]. Studies suggest that 20%-29% of these admissions are unnecessary [23,24]. Unnecessary admissions waste health care resources, overwhelm hospital capacity, increase patient and parental distress, introduce iatrogenic risk such as exposure to other infectious diseases, and expose other hospitalized children to the respiratory pathogens of these patients [11,17,25]. As many as 10% of infants affected by bronchiolitis have adverse events while in the hospital [26]. Similarly, about 6% of ED discharges for bronchiolitis are unsafe, resulting in ED return with hospital admission [27] due to inadequate treatment [11]. New approaches are needed to improve ED disposition decision making and reduce unnecessary admissions and unsafe ED discharges.

One method to reduce practice variation and improve clinicians’ decision making for bronchiolitis care is to use clinical guidelines [28-31]. However, existing clinical guidelines for bronchiolitis acknowledge that decisions to admit or to discharge are subjective and rely on variable clinical judgment due to a lack of specific objective thresholds with good evidence [30,31]. Clinical guidelines also do not account for differences in patient and illness characteristics including comorbidities [32] and offer limited improvement in determining ED disposition.

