For the last 5 years, data captured cover more than 2900 patients under age 2 and 3500 ED encounters for bronchiolitis per year. Due to its attribute richness and large size, the data set provides many advantages in the exploration of the proposed predictive models. Furthermore, we will use 21 environmental variables that regional monitoring stations recorded over the past decade within the Intermountain Healthcare region. These variables include carbon monoxide, nitrogen dioxide, particulate matter up to 2.5 μm in size and 10 μm in size, ozone, sulfur dioxide, relative humidity, temperature, precipitation, wind speed, dew point, and activities of each of the following viruses: enterovirus; adenovirus; parainfluenza virus types 1, 2, and 3; human metapneumovirus; influenza A and B viruses; rhinovirus; and respiratory syncytial virus. The data for all nonvirus environmental variables came from federal data sources [47,48], which provide such data throughout the United States. Observation unit admissions will be treated as hospital admissions since the only pediatric observation unit within Intermountain Healthcare has the same admission, coding, billing, and documentation requirements. Our analysis will consider various attribute combinations to ascertain the minimum requirement on performance and will permit tradeoffs for the adaption of our model beyond our setting dependent upon available attributes. Our analysis results will serve as the basis for future expansion of our models to other clinical data sets and diseases beyond bronchiolitis.

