### Aim 1: Develop an Operational Definition of Appropriate Hospital Admission for ED Patients with Bronchiolitis

In a recent paper [39], we provided a definition framework of appropriate hospital admissions. As shown in Figure 1, we equate appropriate admissions to necessary admissions and unsafe discharges. We equate appropriate ED discharges to safe discharges and unnecessary admissions. The definition uses several threshold values, such as the maximum number of hours for which major medical interventions are used. Using a data-driven approach, we will fill in these values and develop an operational definition to be used in Aims 2 and 3.

For unsafe discharges, we will examine the distribution of the interval between discharge from the ED and a return visit resulting in admission for bronchiolitis within the period of 2 weeks [49,50]. The 95th percentile of the interval will cover most readmissions and define the return threshold for unsafe discharge. The distribution is highly skewed toward a short interval [27]. Thus, the return threshold will be insensitive to the length of the period chosen.

For unnecessary admissions, we will examine the patients who stayed in the hospital for 12 hours or less and were discharged without readmission for bronchiolitis within 2 weeks. These patients are likely to have been admitted unnecessarily. Their median duration of using major medical interventions (Figure 1) will serve as a conservative threshold for use of major medical interventions in all admissions. Unnecessary admissions are those with major medical intervention exposures for no longer than the threshold. We will conduct sensitivity analysis to evaluate the impact of interactions between major medical interventions and other variables.

If the operational definition for all bronchiolitis patients lacks face validity, we will examine data distributions for different age groups to obtain operational definitions by age group. Since the medical interventions for bronchiolitis have not changed over the last 10 years, we would expect the operational definition to remain the same during this period.

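### The years 1–9 cross-validation does not keep a child's visits in one fold, so its AUROC can be optimistic, mainly for nearest neighbour

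*Protocol article*

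**What the plan says.** The validation scheme is in the protocol article under Aim 2, Sample Size Justification and Performance Evaluation: "We will perform stratified 10-fold cross validation [56] on the initial 9 years of data", both for training the models and for estimating how accurate they are. The last year is held back: "Data from the tenth year will be used to evaluate performance of the best-performing machine learning algorithm, reflecting use in practice". The same section counts its test data in visits: "Data from the tenth year include 3615 ED visits for bronchiolitis, which provides adequate power for testing our hypothesis". No unit of fold assignment is named, and nothing keeps one child's visits together.

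The Methods show that children recur: "data captured cover more than 2900 patients under age 2 and 3500 ED encounters for bronchiolitis per year".

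Aim 1 links visits through the outcome. An unsafe discharge depends on the time to "a return visit resulting in admission for bronchiolitis within the period of 2 weeks". For the label, "we equate appropriate admissions to necessary admissions and unsafe discharges". The Introduction gives the frequency: "about 6% of ED discharges for bronchiolitis are unsafe, resulting in ED return with hospital admission".

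Under Predictive Models, k-nearest neighbour and random forest are named candidates. Interpretable models, with k-nearest neighbour as an example, are preferred if their AUROC is at least 0.9 and no more than 0.02 below that of less interpretable ones. Backward elimination also works to 0.02 and 0.9.

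**The concern.** Stratification balances the two outcome classes across folds. It does not keep related records together. If a discharged visit is in the test fold and the same child's return visit is in the training folds, a learner that relies on close matches can recognise the child instead of learning what predicts appropriate admission.

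Similarity within a pair is plausible. Of the structured predictors in Table 1, gender, prematurity, prior intubation, history of bronchopulmonary dysplasia, history of eczema and passive smoking hardly change in two weeks, and age barely moves.

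What is at stake is model development. The tenth year evaluates only the best-performing algorithm, so the choice among algorithms has to be made on years 1–9. Nearest neighbour, the candidate most exposed to this bias, is also among the models that the interpretability rule favours.

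**Working it through.** **The plan's own figures.** The article needs 356 instances per class for the paired AUROC test (one-sided 0.05, 90% power, correlation 0.6, difference 0.05). The baseline AUROC is not stated. With 0.70 assumed, the Hanley–McNeil variance gives 361 or 349, depending on whether the null or the alternative variance is used. Both are within 2% of 356. The Aim 3 figure follows from (1.645 + 1.282)²/0.1² = 856.4, so 857. Neither figure is disputed.

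**Repeat visits** (Methods: more than 2900 patients, 3500 encounters a year).
- Repeats: 3500 − 2900 = 600, and 600/3500 = 17%.
- Visits that share a child with another visit that year: 2 × 600/3500 = 34% if each repeating child has two visits, or 3 × 300/3500 = 26% if each has three. As there are more than 2900 patients, these figures are slightly high. They include repeats that may be months apart.

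**Index–return pairs** (Introduction: 32–40% admitted, 20–29% of admissions unnecessary, 6% of discharges unsafe).
- Unsafe discharges per year: 0.06 × 0.60 × 3500 = 126 to 0.06 × 0.68 × 3500 = 143.
- Positive share of visits, as admitted × necessary + unsafe: lowest 0.32 × 0.71 + 0.0408 = 0.268; highest 0.40 × 0.80 + 0.036 = 0.356.
- Share of positives that belong to a pair, if every return is a necessary admission: 2 × 0.036/0.356 = 20% to 2 × 0.0408/0.268 = 30%.
- The same share, if returns are unnecessary at the general rate: 0.036 × 1.80/0.356 = 18% to 0.0408 × 1.71/0.268 = 26%.

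**Chance that a pair is split.** With ten random folds, two visits fall in different folds with probability of about 1 − 1/10 = 90%.

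**Size of the bias.** The article gives no within-child similarity, so three simulations compared 10-fold AUROC with folds drawn by visit and by child, under assumed values.
- *3500 visits, 139 same-label pairs, feature correlation 0.5–0.8, 4 replicates.* Nearest neighbour 0.68–0.69 by visit against 0.62–0.63 by child; random forest 0.774–0.797 against 0.746–0.754; logistic 0.78 against 0.77–0.78. At 0.8 the forest led under visit folds and the logistic model under child folds.
- *1.21 visits per child, pairs not modelled separately.* 5-nearest neighbour differed by about 0 under weak similarity, by 0.667 − 0.643 = 0.024 with 30 fixed child attributes and residual child correlation 0.5, and by 0.800 − 0.755 = 0.045 when a child's visits were near-duplicates. The forest differed by at most 0.807 − 0.797 = 0.010 and logistic by at most 0.002. No ranking changed. One of five planned scenarios in the part that included the forest did not finish.
- *17 features, 139 pairs, 75.5% of returns positive, 3 replicates.* 5-nearest neighbour 0.666 against 0.647 at correlation 0.8, and 0.670 against 0.647 at 0.9. Forest 0.758 against 0.746 at 0.9. Logistic was unchanged, and bias was about zero at 0.3. Larger runs with 60 features did not finish.

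**Tenth-year tests.** Expected positives are 0.268 × 3615 = 969 to 0.356 × 3615 = 1287. With Poisson extra visits (mean 0.207 per child), the largest clustering factor is (1.207² + 0.207)/1.207 = 1.38. Then 969/1.38 ≈ 700 effective positives against 356 needed, and 3615/1.38 ≈ 2600 visits against 857. Standard errors could be too small by a factor of up to about √1.38 = 1.17.

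**The case against.** Much of the case on the other side stands.

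- **The article does not say that folds are drawn by visit.** This is inferred from the named scheme and the unit of counting. A condensed article may leave fold detail to a fuller plan. Even so, it names a specific scheme, and that scheme in its ordinary form does not protect against a link that the outcome definition creates.
- **A reader might infer that the study's final accuracy will be inflated.** The documents do not support that. The AUROC hypothesis and the Aim 3 impact estimates use the tenth year, which is separated by time. Only children seen on both sides of the year 9/10 boundary overlap, and such overlap would also occur in practice.
- **A reader might infer that the wrong algorithm will be chosen.** A reversal appeared in one setting of one simulation with four replicates. Nearest neighbour, even when inflated, stayed well below the logistic model there.
- **Similarity within pairs is assumed.** SpO2, heart rate, respiratory rate and temperature can change between a discharge and a return that ends in admission.
- **The simulations are not at the plan's operating point.** All their AUROCs are below 0.9, where the interpretability rule does not apply, and backward elimination was not simulated. The article also does not say which AUROC drives those two rules. The first simulation covered about one year of visits, and bias at nine-year size is untested.
- **Not every pair leaks.** Some returns will be classed as unnecessary admissions and carry the opposite label, and a few pairs straddle years 9 and 10.

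**Conclusion.** The point holds for the cross-validation on years 1–9. Run in its ordinary form on visit-level data, the stated scheme separates about 90% of linked pairs, and visits in such pairs make up roughly 18–30% of the positive class on the article's cited rates. The resulting optimism in AUROC is about 0 to 0.07 for nearest neighbour, up to about 0.04 for random forest, and 0.01 or less for logistic regression. Where a value falls in that range depends on within-child similarity, which the article does not give; with weak similarity the bias vanishes. For nearest neighbour it can exceed the 0.02 margin, so it could sway algorithm choice and tuning. That remains a possibility, not a demonstrated error.

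A smaller point also holds: the tenth-year Z-test, t-test and McNemar's test, as described, make no allowance for repeat visits, so standard errors may be somewhat too small. It would be wrong to read this as a shortage of power, since both sample-size requirements are met with room to spare after the largest clustering allowance.

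**What to change.** State that the ten folds are assigned by child, stratified on the outcome as closely as grouping allows, so that all visits of a child in years 1–9 stay in one fold. Use these folds for algorithm comparison and tuning, and for backward elimination where it relies on cross-validation. For the tenth-year tests, use standard errors clustered by child, for example from a bootstrap that resamples children.

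This needs a study identifier for each child in the fold assignment. The de-identified data must already link a child's visits in order to find returns, so no new data are needed. The cost is a possibly lower cross-validated AUROC and slightly wider intervals. The tenth-year hold-out and the sample sizes need no change.

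### The anticipated current-care AUROC (0.6 to 0.8+) does not follow from the rates it is said to rest on; these give about 0.86-0.89, against which a model at or just above the 0.9 target would miss the hypothesised 0.05 gain

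*Protocol article*

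**What the plan says.** All of this is in the Protocol article.

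- **Anticipated baseline** (Aim 2, Sample Size Justification and Performance Evaluation): "we anticipate the AUROC achieved by current care to be between 0.6 and 0.8", followed by a plus sign. The stated basis is an extrapolation from "unnecessary admissions up to 29% and unsafe ED discharges of 6" per cent, with several references.
- **Denominators** (Introduction): "About 32%-40% of ED patients with bronchiolitis are admitted to the hospital"; "Studies suggest that 20%-29% of these admissions are unnecessary"; "about 6% of ED discharges for bronchiolitis are unsafe".
- **Outcome classes** (Aim 1): "we equate appropriate admissions to necessary admissions and unsafe discharges". Safe discharges and unnecessary admissions form the other class.
- **Target** (Predictive Models): "Our target will be models achieving an AUROC larger than or equal to 0.9". An interpretable model is preferred if it reaches 0.9 and is at most 0.02 worse than a less interpretable one.
- **Pruning** (Sample Size Justification): backward elimination continues while the AUROC falls by no more than 0.02 and stays at 0.9 or above.
- **Hypothesis and size** (same section): the model is to exceed current care by at least 0.05 in AUROC, and "a sample size of 356 instances per possible value of the dependent variable will have 90% power to detect an AUROC increase of 0.05", with correlation 0.6 and a 1-sided 0.05 test. Year ten has 3615 visits.

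**The concern.** The range is presented as a consequence of two error rates. Together with the admission rate, those rates determine the AUROC of a yes/no decision, so the range can be checked, and its lower end looks far too low.

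Three figures have to fit together: the expected baseline, the 0.9 target and the 0.05 gain. With a baseline of 0.6 to 0.8, any model reaching 0.9 clears the gain easily, and 0.9 is a safe working floor. If the named rates imply a higher baseline, 0.9 no longer secures the gain. The model-selection rules, which look only at 0.9 and at a 0.02 loss, could then settle on a model that reaches the target and misses the hypothesis. The plan does not say which criterion governs in that case.

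**Working it through.** **1. The plan's own sample size.** The baseline AUROC behind 356 per class is not stated, so I scanned it. For a paired comparison with r = 0.6, 1-sided 0.05, 90% power and difference 0.05:

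n = [z(0.95)·√V0 + z(0.90)·√V1]² / 0.05²

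V0 and V1 are the variances of the AUROC difference (scaled per class) under the null and the alternative. The ranges below are with and without a separate null variance.

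| Variance formula | Baseline | n per class |
|---|---|---|
| Hanley-McNeil | 0.70 | 348-360 |
| Full binormal | 0.70 | 350-360 |
| Obuchowski approximation | 0.75 | 349-361 |
| Hanley-McNeil to Obuchowski | 0.86 | about 165-240 |

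The figure of 356 is therefore consistent with a baseline of about 0.70-0.75, inside the stated range.

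**2. Current care from the named rates.** Let a be the admission rate (0.32-0.40), u the unnecessary share of admissions (0.20-0.29) and f the unsafe share of discharges (0.06). As shares of all visits:

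- true positives (necessary admissions) = a(1 − u)
- false positives (unnecessary admissions) = a·u
- false negatives (unsafe discharges) = (1 − a)f
- true negatives (safe discharges) = (1 − a)(1 − f)

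A single yes/no decision has AUROC = (sensitivity + specificity)/2.

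Example with a = 0.40, u = 0.29: the cells are 0.284, 0.116, 0.036 and 0.564. Sensitivity = 0.284/0.320 = 0.8875, specificity = 0.564/0.680 = 0.8294, and AUROC = 0.8585.

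| a | u | Sensitivity | Specificity | AUROC | AUROC + 0.05 | 0.90 − AUROC |
|---|---|---|---|---|---|---|
| 0.32 | 0.29 | 0.8478 | 0.8732 | 0.8605 | 0.9105 | 0.0395 |
| 0.36 | 0.29 | 0.8694 | 0.8521 | 0.8608 | 0.9108 | 0.0392 |
| 0.40 | 0.29 | 0.8875 | 0.8294 | 0.8585 | 0.9085 | 0.0415 |
| 0.32 | 0.20 | 0.8625 | 0.9090 | 0.8858 | 0.9358 | 0.0142 |
| 0.36 | 0.20 | 0.8824 | 0.8931 | 0.8877 | 0.9377 | 0.0123 |
| 0.40 | 0.20 | 0.8989 | 0.8758 | 0.8873 | 0.9373 | 0.0127 |

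The range is 0.86-0.89. Since 29% is the stated maximum, 0.86 is the pessimistic end.

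**3. What would give lower values.** With f = 0.06, an AUROC of 0.80 needs 48%-49% of admissions to be unnecessary, and 0.60 needs about 87%. Raising both rates, 0.59-0.60 needs about 50% unnecessary and 30% unsafe. Two misreadings of the inputs also stay well above 0.6:

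- Averaging 1 − 0.29 and 1 − 0.06 gives 0.825, but these are predictive values, so the mean is not an AUROC.
- Taking the 6% as a share of all visits, against the Introduction, gives 0.82-0.86.

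**4. Target against hypothesis.** A model at 0.90 gains 0.012-0.042. A gain of 0.05 needs about 0.91 (u = 0.29) to 0.94 (u = 0.20). With 3615 visits and r = 0.6, the chance that a model truly at 0.90 shows an observed gain of 0.05 is at most about 10%, and near zero at u = 0.20.

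**5. Effect of the floors.** Take a baseline of 0.8605. A model at 0.92 gains 0.0595. Backward elimination, or a switch to an interpretable model, may cost 0.02 and stop at 0.90, where the gain is 0.0395. Both rules are satisfied and the 0.05 is lost.

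**6. Year-ten numbers.** The positive share a(1 − u) + (1 − a)f runs from 0.268 to 0.356. Times 3615, that is about 970 to 1290 positives, well above 356.

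**The case against.** - **The upper limit is open-ended.** The plus sign literally admits 0.86-0.89. This stands: the range does not exclude the derived value. What lacks support is the 0.6 end and the stretch up to about 0.86.
- **The target is a floor.** A reader might infer that a model meeting the target cannot show the 0.05 gain. The document does not support that. The target is 0.9 or more, so a model at about 0.91-0.94 or above meets both criteria. The shortfall applies at or just above 0.90.
- **The test may be against zero.** If 0.05 is only the design alternative, a model at 0.90 would still be shown better than current care, with power from about 64% to nearly 100% at 3615 visits. This stands too, but the hypothesis as worded is a gain of at least 0.05.
- **The derivation is conditional.** The protocol calls its range an extrapolation, says that no such AUROC has been reported, and cites sources not at hand. The cohort's labels await the Aim 1 thresholds. So 0.86-0.89 is what the named rates imply, not a prediction for this cohort. The text nevertheless names no other rates as the basis.
- **The pruned model may not be the one tested.** The article does not say whether the pruned or interpretable model carries the year-ten comparison. The effect of the floors matters if it does.

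**Conclusion.** The point holds at moderate severity. On the document's own rates and denominators, current care scored as a yes/no decision has an AUROC of about 0.86-0.89. Most of the anticipated range does not follow from its stated basis. A model only just at target would gain about 0.01-0.04 rather than 0.05, and no selection rule protects the 0.05. The conclusion assumes that the literature rates apply to this cohort and to the labels that Aim 1 will produce.

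Two stronger readings are not supported. One is that 356 per class is wrong or that the study lacks power. The figure reproduces at a baseline of about 0.70-0.75, fewer are needed near 0.86, and year ten supplies about 970-1290 positives. More than 356 would be needed only toward the low end (about 420-430 at 0.60 by the Hanley-McNeil and Obuchowski formulas), which the named rates do not reach. The defect here is only that the baseline is unstated.

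The other is that the two prior models cited are no better than implied current care. Their reference standards differ from appropriate admission, as the protocol itself says, so the figures are not comparable.

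**What to change.** 1. Show the 2x2 table and restate the anticipated current-care AUROC as about 0.86-0.89 if the literature rates hold in this cohort. Otherwise give the further figures that lead to 0.6.
2. State that a 0.05 gain then needs a model AUROC of about 0.91-0.94.
3. Tie the target, the backward-elimination floor and the interpretability floor to the larger of 0.9 and current care plus 0.05, with current care estimated on the nine training years so that year ten stays untouched. Alternatively keep 0.9 and state that it alone is not expected to show the 0.05 gain.
4. State the baseline AUROC behind 356 per class.

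The cost is a rewritten paragraph and two amended selection rules. No further data are needed, though the stated expectations become less favourable. It is best settled before year-ten results are seen.
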